## Abstract

**Background:**

Pragmatic cluster-randomised trials should seek to make unbiased estimates of effect and be reported according to CONSORT principles, and the study population should be representative of the target population. This is challenging when conducting trials amongst ‘hidden’ populations without a sample frame. We describe a pair-matched cluster-randomised trial of a combination HIV-prevention intervention to reduce the proportion of female sex workers (FSW) with a detectable HIV viral load in Zimbabwe, recruiting via respondent driven sampling (RDS).

**Methods:**

We will cross-sectionally survey approximately 200 FSW at baseline and at endline to characterise each of 14 sites. RDS is a variant of chain referral sampling and has been adapted to approximate random sampling. Primary analysis will use the ‘RDS-2’ method to estimate cluster summaries and will adapt Hayes and Moulton’s ‘2-step’ method to adjust effect estimates for individual-level confounders and further adjust for cluster baseline prevalence. We will adapt CONSORT to accommodate RDS. In the absence of observable refusal rates, we will compare the recruitment process between matched pairs. We will need to investigate whether cluster-specific recruitment or the intervention itself affects the accuracy of the RDS estimation process, potentially causing differential biases. To do this, we will calculate RDS-diagnostic statistics for each cluster at each time point and compare these statistics within matched pairs and time points. Sensitivity analyses will assess the impact of potential biases arising from assumptions made by the RDS-2 estimation.

**Discussion:**

We are not aware of any other completed pragmatic cluster RCTs that are recruiting participants using RDS. Our statistical design and analysis approach seeks to transparently document participant recruitment and allow an assessment of the representativeness of the study to the target population, a key aspect of pragmatic trials. The challenges we have faced in the design of this trial are likely to be shared in other contexts aiming to serve the needs of legally and/or socially marginalised populations for which no sampling frame exists and especially when the social networks of participants are both the target of intervention and the means of recruitment.

The trial was registered at Pan African Clinical Trials Registry (PACTR201312000722390) on 9 December 2013.

## Background

HIV/AIDS remains a public health problem of unprecedented scale in many low- and middle-income countries, particularly in southern Africa. Incidence has peaked in many countries but remains unacceptably high at an estimated 1.5 million across sub-Saharan Africa in 2013. Similarly, treatment has expanded, but a wide gap exists in treatment: only 29 % of those who are HIV positive in the region are estimated to be virally suppressed, and 1.1 million HIV-related deaths occurred in sub-Saharan Africa in 2013 [1]. Increasingly, the challenge is in finding models of intervention that can be successfully implemented at scale to ensure universal, equitable access to effective treatment and prevention technologies.

In many sub-Saharan African countries, female sex workers (FSW) and their clients remain at very high risk of acquiring HIV [2], and may have reduced access to treatment [2]. In Zimbabwe, data from 2009 to 2013 suggest greater than 10 % annual HIV incidence among FSW [3], that only 67 % are aware of their HIV status and that 49.5 % of all FSW testing positive for HIV have a viral load < 1000 copies/ml ([name], et al. HIV care cascade among female sex workers in Zimbabwe: baseline results of the SAPPH-IRe Trial, submitted). While guidelines for interventions for FSW exist [4], few impact evaluations have addressed how effective such approaches are in practice.

Pragmatic trials seek to estimate population-level intervention or programme effectiveness on target groups under real-life delivery conditions. This leads to a focus in pragmatic trials on *less* researcher-led control of intervention delivery, but a *stronger* requirement to measure fidelity of intervention implementation [5]. Pragmatic trials also seek to maximise the representativeness of the research sample to the source population. These requirements of the pragmatic trials raise particular challenges for their design and analysis, especially where the target population is hidden or marginalised, as is the case for FSW in southern Africa.

The SAPPH-IRe trial in Zimbabwe (‘Sisters Antiretroviral Programme for Prevention of HIV – an Integrated Response’) was initiated in April 2014. The aim of the trial is to estimate the effect of a combination intervention package on the proportion of Zimbabwean FSW who have an HIV viral load ≥ 1000 copies/ml (approximately reflecting whether a person is infectious). The trial is designed as a pragmatic cluster randomised trial with several novel features including recruitment via respondent-driven sampling (RDS). RDS is a variant of chain referral sampling, for which a model of sampling probabilities is applied and used to weight the data to approximate random sampling. This paper outlines the design of the trial, and reports our analysis plan designed to reflect CONSORT principles.

## Interventions

Since 2009, the national ‘Sisters’ programme has provided targeted HIV services for FSW across all regions of Zimbabwe in line with WHO guidelines [4]. This set of services is the usual standard of care available to comparison communities in the SAPPH-IRe trial. The program provides free condoms and contraception, HIV testing and counselling, syndromic management of sexually transmitted infections, and legal advice supported by a network of peer educators. New standard-of-care services being introduced over the trial period include providing long-acting reversible contraception, community mobilisation and real-time electronic data collection. The ‘Sisters’ programme is run by programme staff through dedicated drop-in centres based at primary care clinics at FSW hotspots around the country. Women who require HIV care and/or antiretroviral treatment (ART) are referred to government services.

In the SAPPH-IRe intervention arm, we will enhance access to ART for HIV prevention and treatment for FSW. We are using enhanced community mobilisation to foster an empowering environment and increase uptake of HIV testing, prevention and treatment services. Targeted activities actively engage women in prevention and treatment by (1) raising awareness of the benefits and availability of ARV drugs for treatment and also for pre-exposure prophylaxis (PrEP); (2) strengthening networks of support to encourage health-promoting behaviour, including the promotion of antiretroviral adherence; and (3) building leadership skills among FSW. For women who access services and test HIV-negative, we are implementing a programme of activities designed to increase repeat HIV testing, including with the use of SMS messaging reminders. On the supply side we enhance on-site clinical services to make ARV for treatment and prevention more readily available to FSW [6]. We include an offer of PrEP for HIV-negative FSW, on-site initiation of ART in line with internationally accepted guidelines for those who have tested HIV-positive, and clinical and social support services delivered by clinical staff within this package [7].

## Methods/Design

### Design

The trial is a matched, cluster randomised controlled trial, Fig. 1. Trial sites have been purposively selected to be reflective of a range of settings, they are of adequate size to ensure participation of between 85 and 300 new FSW annually, and they are located at geographic spacing sufficient to ensure that the risk of contamination/spill-over of intervention effect between study clusters through FSW mobility and migration is minimised. A cluster was defined as the FSW population working in the geographic location around a government health clinic where dedicated FSW services are being delivered.

**Fig. 1 Fig1:**
[figure not shown]
Summary of trial design

### Matching and randomisation

Trial sites were pair-matched on the basis of the setting (for example, town, growth point and colliery/army base) and whether the site had been providing dedicated FSW services since 2009/10 or was a newer outreach site. We conducted a public randomisation on 31 January 2014 and invited a number of stakeholders, including national and provincial representatives of Ministry of Health and Child Care National AIDS Council and the trial community advisory board. The randomization was performed by inviting non-investigator attendees to draw from a bag the name of one of the sites from each pair. The draw for each pair was performed by a different stakeholder. The first names that were drawn were designated to group 1, and the names of sites left in the bag, to group 2. Finally a coin was first inspected, and then through a toss of this coin, the sites in “group 2” were allocated to the enhanced intervention arm and those in “group 1” to the usual care arm.

### Primary and secondary endpoints

The trial endpoint is the proportion of all FSW who have an HIV viral load ≥ 1000 copies/ml (approximately reflecting whether a person is infectious). This has been assessed at baseline December 2013 and will be assessed again at endline in April/May 2016. The FSW will be recruited using RDS, as described below.

### Sample size calculations

We enrolled 14 clusters in seven matched pairs in both the baseline and final RDS surveys, aiming to recruit 200 FSW at each site. We used the approach of Hayes and Bennett [8] to determine an appropriate sample size. RDS estimates can have high variance [9, 10], which translates to greater variation between cluster prevalence estimates in our analysis. Given the estimated prevalence of HIV and access to care at baseline, our estimate of intervention effect and the 14 clusters of approximately 200 FSW per site, we calculated that the matched-pair coefficient of variation could be up to k_m_ = 0.2, to achieve 80 % power ([name]: Antiretrovirals for HIV prevention and treatment among Zimbabwean sex workers, unpublished) (Fig. 2).

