**Fig. 2 Fig2:**
[figure not shown]
Sample size considerations for the SAPPH-IRe Trial. Notes: (**a**) We estimated that in the comparison arm 41 % of SW will have a detectable viral load at 24 months. The breakdown of hypothesised effect of the intervention on HIV prevalence, the proportion of HIV infected women who are diagnosed, the proportion of diagnosed women who are on ART, and the proportion of women on ART with detectable viral load is shown in Table 2. We hypothesize that with realistic estimates of the size of the potential effect of our intervention on improving knowledge of HIV status among HIV-infected SW, decreasing time to treatment initiation and improving adherence, in the enhanced intervention arm (Arm B) 28 % of SW should be expected to have detectable viral load at the time of the final RDS survey. We also show more ‘optimistic’ and ‘pessimistic’ scenarios. (**b**) Number of matched paired of SW clinics (clusters) and number of women per site required to detect a reduction in proportion of women not virally suppressed (not on ART or virologically failing) from 41 to 28 % (80 % power, 5 % level of significance) for various values of the between-cluster coefficient of variation (km) in the proportion not virally suppressed within matched pairs. (**c**) Power and between-cluster coefficient of variation (km) in the proportion not virally suppressed within matched pairs for different scenarios for realistic, optimistic and pessimistic hypothesised intervention effects with 7 pairs of matched pairs and 200 women per cluster (5 % level of significance)

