We recognise that there are potential limitations and threats to the research. The need to minimise contamination between communities has meant that we have only 14 clusters, which could make finding an effect challenging. While RDS weighting is intended to reduce bias in chain referral sampling, simulation and empirical studies have shown that variance around the weighted point estimates for each cluster could be very high [9, 10]. In our study, this variance will be reflected in the between-cluster differences. Our power calculations have accounted for a between-matched-pair coefficient of up to 0.19, and at baseline we calculated k_m_ to be 0.18 ([name], et al. HIV care cascade among female sex workers in Zimbabwe: baseline results of the SAPPH-IRe Trial, submitted). Additionally, we have sought to improve power by matching sites and adjusting our final analysis by baseline age and education characteristics.

While our aim of assessing the intervention under routine conditions makes recruiting a representative sample of FSW important, this is challenging when we lack a sample frame. We have sought to address this problem by using RDS, but we recognise that this is not a panacea in delivering unbiased representative estimates. Often RDS is implemented variably, limiting comparability. A strength of our study is the identical protocol implemented at each study site. We are aware of one other application of RDS in a cluster randomised trial, but to our knowledge no trials have yet been completed [34, 35]. We have described a range of potential biases that can arise from differences in the assumed and real sampling process under RDS. We have adapted our surveys to collect the information required to signal whether any of these biases could be present, and we have planned sensitivity analyses to assess their impact on our study findings.

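### The sample size section's k_m limit of 0.2 gives about 75% power, not 80%, under the cited matched-pair formula, and conflicts with the 0.19 in the Discussion

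*Protocol article*

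**What the plan says.** The Sample size calculations section gives the design: "We enrolled 14 clusters in seven matched pairs in both the baseline and final RDS surveys, aiming to recruit 200 FSW at each site". It names the method, "We used the approach of Hayes and Bennett [8] to determine an appropriate sample size", and then gives the limit on variation: "we calculated that the matched-pair coefficient of variation could be up to k_m" = 0.2, for 80% power.

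The Fig. 2 legend supplies the proportions. For the comparison arm, "We estimated that in the comparison arm 41 % of SW will have a detectable viral load at 24 months". For the intervention arm, "28 % of SW should be expected to have detectable viral load at the time of the final RDS survey". It repeats 80% power, 5% significance, 7 pairs and 200 women per cluster. It presents the calculation "for various values of the between-cluster coefficient of variation (km) in the proportion not virally suppressed within matched pairs", so k_m is variation between clusters inside a pair.

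The Discussion gives another limit: "Our power calculations have accounted for a between-matched-pair coefficient of up to 0.19". The same sentence reports a baseline k_m of 0.18.

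**The concern.** One design has two limits on k_m, 0.2 and 0.19, and nothing reconciles them. In a trial of seven pairs the between-cluster term dominates the variance, so a step of 0.01 in k_m moves power by more than 3 percentage points. The limit is also what a reader sets against the observed baseline value of 0.18. Against 0.2 the headroom looks like 0.02. Against the limit that the cited formula supports, it is about 0.006. A reader who relies on the sample size section would credit the trial with more tolerance for between-cluster variation than it has.

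There is a smaller wording problem. The Discussion's label can be read as variation between pairs, whereas the legend defines k_m as variation between clusters within pairs.

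**Working it through.** **Inputs.** p0 = 0.41 and p1 = 0.28 (Fig. 2 legend); m = 200 women per cluster and c = 7 pairs (Sample size calculations, Fig. 2 legend); 80% power and 5% significance (Fig. 2 legend). The sample size text does not state sidedness. Two-sided is taken from the decision rule under Analysis principles, which asks whether the 95% confidence interval excludes 1. Hence z = 1.960 and 0.842, and (1.960 + 0.842)² = 7.849.

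**Formula (Hayes and Bennett, pair-matched).**

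R(k) = [p0(1−p0)/m + p1(1−p1)/m + k²(p0² + p1²)] / (p0−p1)²

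Pairs needed = 2 + 7.849 × R(k)

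Power with 7 pairs = Φ(√(5/R(k)) − 1.960), where 5 = 7 − 2

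**Fixed parts.**
- Sampling term: (0.41×0.59 + 0.28×0.72)/200 = (0.2419 + 0.2016)/200 = 0.0022175
- Multiplier of k²: 0.41² + 0.28² = 0.1681 + 0.0784 = 0.2465
- Denominator: 0.13² = 0.0169

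**The plan's own figure, k_m = 0.20.** R = (0.0022175 + 0.04×0.2465)/0.0169 = 0.0120775/0.0169 = 0.7146. Pairs needed = 2 + 7.849×0.7146 = 7.61. Power with 7 pairs = Φ(√(5/0.7146) − 1.960) = Φ(0.685) = 75.3%. The stated 80% is not reproduced.

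**Other values of k_m.**

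| k_m | Source | R | Pairs needed | Power, 7 pairs |
|---|---|---|---|---|
| 0.18 | Baseline value, Discussion | 0.6038 | 6.74 | 82.1% |
| 0.19 | Limit in Discussion | 0.6578 | 7.16 | 78.7% |
| 0.20 | Limit in Sample size calculations | 0.7146 | 7.61 | 75.3% |

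**Limit for exactly 80% with 7 pairs.** R must equal 5/7.849 = 0.6370. Then k² = (0.6370×0.0169 − 0.0022175)/0.2465 = 0.0347, so k = 0.186, or 0.19 to two decimals.

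**Does the result depend on the variant?** At k_m = 0.20:
- Paired t-test with noncentral t, 6 df: 74.2% (80% limit 0.183).
- Same formula on the log-ratio scale: 76.9%.
- Unmatched correction (+1 in place of +2): 82.6% (limit 0.208).
- Unpaired t-test, 12 df: 81.9%.
- One-sided 5%: 84.1%.

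The variants that reach 80% at 0.20 drop either the matching or the two-sided test, and so do not fit the stated design.

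**Does rounding of the proportions rescue 0.20?** Each proportion was moved by up to half a point:

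| p0 vs p1 | Power at k_m 0.20 | 80% limit |
|---|---|---|
| 41.5% vs 27.5% | 81.1% | 0.204 |
| 41% vs 27.5% | 78.8% | 0.196 |
| 41.5% vs 28% | 77.9% | 0.194 |
| 41% vs 28% | 75.3% | 0.186 |
| 40.5% vs 28.5% | about 69% | 0.168 |

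Of the nine combinations tried (each proportion at its printed value and half a point either side), only the one with both proportions at their favourable extreme reaches 80% at 0.20.

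**The case against.** The best defence is rounding. A limit of 0.186 is 0.19 to two decimals and 0.2 to one, so the two sections may print the same number at different precision. The 41% and 28% are themselves whole-number results of a cascade whose table is not in the text available, and inputs within rounding give limits from 0.168 to 0.204. The panels of Fig. 2, which show the original calculation, could not be inspected.

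Much of this stands. It clears the Discussion: 0.19 is what the cited formula returns to two decimals. It also means that 0.186 should not be presented as more precise than its inputs. It does not clear the 0.2. That figure is worded as a maximum, and rounding a maximum tolerable variation upward errs in the favourable direction, here by about 5 points of power. Two-decimal precision was available, since the Discussion uses it.

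Three stronger inferences are tempting, and the document does not support them:

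- **The Discussion's 0.19 is wrong too.** It agrees with the formula to the precision printed, at about 79% power.
- **The planned regression, which also adjusts for baseline and so has 5 residual df, makes power materially lower.** That assumes the baseline cluster summary explains nothing, which is the worst case for the same outcome measured at the same sites. The +2 in the formula is the cited method's own small-sample allowance.
- **The baseline k_m of 0.18 is too imprecise to rely on.** The article claims no particular precision for it, so there is nothing to contradict.

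**Conclusion.** The point holds for the sample size section. On the stated inputs, 7 pairs of 200 give about 75% power at k_m = 0.20, and 80% power holds only up to about 0.186. The 0.2 overstates the tolerable variation and conflicts with the Discussion's 0.19, which is essentially right. This rests on a two-sided 5% test, the matched-pair form of the cited method, and 41% and 28% taken as printed.

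The impact is modest. A reader might infer that the trial is underpowered, but the document does not show that: at its reported baseline k_m of 0.18 the same formula gives about 82%, and the paired t-test with 6 df about 81%. What changes is the margin, which is thin. The Discussion already hints at this by setting 0.18 beside 0.19. Its between-matched-pair label is loose wording on which no calculation depends.

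**What to change.** In Sample size calculations, replace the 0.2 statement with wording such as: *seven pairs of 200 women give 80% power (41% versus 28%, two-sided 5%) for k_m up to about 0.19 (0.186 on the rounded inputs); power is about 82% at the baseline k_m of 0.18 and about 75% at 0.20.* Use the same limit in the Discussion, and describe k_m there as between-cluster variation within matched pairs, as in the Fig. 2 legend. If 0.2 came from unrounded proportions or from the unmatched correction, say so and show the inputs.

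The cost is a text correction. It needs no extra clusters or women and no change to the analysis. The stated tolerance becomes slightly less favourable.

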**Fig. 2 Fig2:**
[figure not shown]
Sample size considerations for the SAPPH-IRe Trial. Notes: (**a**) We estimated that in the comparison arm 41 % of SW will have a detectable viral load at 24 months. The breakdown of hypothesised effect of the intervention on HIV prevalence, the proportion of HIV infected women who are diagnosed, the proportion of diagnosed women who are on ART, and the proportion of women on ART with detectable viral load is shown in Table 2. We hypothesize that with realistic estimates of the size of the potential effect of our intervention on improving knowledge of HIV status among HIV-infected SW, decreasing time to treatment initiation and improving adherence, in the enhanced intervention arm (Arm B) 28 % of SW should be expected to have detectable viral load at the time of the final RDS survey. We also show more ‘optimistic’ and ‘pessimistic’ scenarios. (**b**) Number of matched paired of SW clinics (clusters) and number of women per site required to detect a reduction in proportion of women not virally suppressed (not on ART or virologically failing) from 41 to 28 % (80 % power, 5 % level of significance) for various values of the between-cluster coefficient of variation (km) in the proportion not virally suppressed within matched pairs. (**c**) Power and between-cluster coefficient of variation (km) in the proportion not virally suppressed within matched pairs for different scenarios for realistic, optimistic and pessimistic hypothesised intervention effects with 7 pairs of matched pairs and 200 women per cluster (5 % level of significance)

### Additional trial components

Process evaluation will include both the qualitative and quantitative assessment of i) whether intervention activities were conducted as scheduled; ii) ‘sex worker friendliness’ toward outreach clinics; and iii) levels of FSW participation in the intervention. We do not describe this data collection in any further detail in this paper. We will also determine the cost of the intervention components and the cost–effectiveness of the enhanced intervention, taking into account the potential reduction in transmissions via transactional sex due to the reduction in the proportion of FSW who are infectious. For this, we will use an existing individual-based dynamic stochastic model to predict the potential impact of this intervention on HIV incidence in the population of Zimbabwe. Again, these methods are not discussed further here.

